### Ethical considerations

Operational approval for the study has been provided by the Director of Nursing at the hospital. Ethics approval has been obtained from the hospital’s Human Research Ethics Committee and Deakin University. Prior to commencement of the study, permission will be sought from the Nurse Unit Managers of the selected wards in order to access staff. This is a minimal risk study.

### Expected outcomes

We expect that this knowledge translation feedback intervention will result in improved quality and frequency of reporting of medication errors. This will enable us to understand the scale and nature of medication errors occurring in the intervention units. Our intent is to produce a parsimonious, efficient and effective method of providing feedback to health professionals about a quality-related measure of practice. We anticipate that this project will result in the development of a feedback approach that can be adapted for and evaluated in other healthcare settings and for additional areas of preventable adverse events. Importantly, this study is designed to add to the body of knowledge about how, when and in what context feedback works best.

### Strengths and limitations of study

This study will add to the evidence base on use of audit with feedback among nurses. In particular, it will promote understanding of the potential for feedback to promote behaviour change regarding medication error reporting, how and in what forms nurses prefer to receive feedback and how the contexts in which nurses work affect their ability to report medication errors. Additionally, the study will contribute knowledge about the accuracy of medication error reporting, comparing hospital incident reporting system data with evidence of administration errors in medical record documentation.

Limitations of this study need to be acknowledged. The study is to be conducted at a single site, with a relatively small sample. While we will match intervention and control wards as closely as possible on the basis of clinical casemix, there is no guarantee that matched wards within the same hospital will be entirely similar (e.g*.*, differences in ward culture, patient acuity/type, staffing turnover); hence, we will adjust for differences using the available data. Feedback will be constructed based upon advice from the key stakeholder group. It is possible that this format will not suit all nurses, and so, some staff may not find the feedback meets their needs and may discount it as a result. Behaviour change in reporting may also occur as a result of other variables (such as policy changes and/or serious medication incidents that make staff more aware/anxious about reporting). Hence, not all behaviour change may be attributable to the feedback intervention. Potential for contamination of the control group exists; however, the organisation has a stable nursing workforce with a vacancy rate of less than 5 %. Thus, permanent staff do not commonly work across different wards, thereby limiting the risk of contamination.

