**Methods/design:**

A quasi-experimental design, incorporating two pairs of matched wards at an acute care hospital, is used. Randomisation occurs at the ward level; one ward from each pair is randomised to receive the intervention. A key stakeholder reference group informs the design and delivery of the feedback intervention. Nurses on the intervention wards receive the feedback intervention (feedback of analysed audit data) on a quarterly basis for 12 months. Data for the feedback intervention come from medication documentation point-prevalence audits and weekly reports on routinely collected medication error data. Weekly reports on these data are obtained for the control wards. A controlled interrupted time series analysis is used to evaluate the effect of the feedback intervention. Self-report data are also collected from nurses on all four wards at baseline and at completion of the intervention to elicit their perceptions of the work context. Additionally, following each feedback cycle, nurses on the intervention wards are invited to complete a survey to evaluate the feedback and to establish their intentions to change their reporting behaviour. To assess sustainability of the intervention, at 6 months following completion of the intervention a point-prevalence chart audit is undertaken and a report of routinely collected medication errors for the previous 6 months is obtained. This intervention will have wider application for delivery of feedback to promote behaviour change for other areas of preventable error and adverse events.

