## Methods

This controlled interrupted time series study design incorporates two pairs of matched wards at an acute care hospital with randomisation of two wards to the control group and two wards to the intervention group. Nurses in the intervention group will receive the SMART intervention (feedback of medication error audit data).

We will adopt the National Coordinating Council for Medication Error Reporting and Prevention standard definition of a medication error: “any preventable event that may cause or lead to inappropriate medication use or patient harm while the medication is in the control of the health care professional, patient, or consumer” [47].

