### Setting and sample

This study will take place at a large, not-for-profit Australian private health provider. Four acute care wards will be included in the study. The wards will be matched as closely as possible according to clinical casemix (diagnostic group and average length of stay).

A key stakeholder reference group will be established to determine the preferred feedback methods and mechanism (the design of the feedback report and how it is presented to staff). This group was instrumental to feedback design in the pilot study and will include clinical nurses and representatives from nursing management, pharmacy and medicine (*n* = 10).

Managers (*n* = 4) and nurses (*n* = 160) working in the four participating wards will be invited to participate in this study.

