### Analysis

Quantitative methods will be used to analyse the survey data. Analysis will involve the use of simple descriptive statistics, including frequencies and cross tabulations, and bivariate analysis using correlations. Interrupted time series analysis will be used to assess for change over time in response to the feedback. Outcomes will include error rates identified during the point-prevalence chart audits and the error report rates identified from RiskMan data. These data will be aggregated at ward level.

We will also examine RiskMan data for the 12-month period prior to the intervention. Intervention dose will be the main predictor, operationalised as the number of nurses on the ward who self-report reading the feedback reports. Aggregated at ward level, scores for the eight dimensions of organisational context will also be included as predictors of medication error reporting rates. Multivariate regression analyses will include cluster correction to adjust for ward and site effect. Content analysis will be used to analyse string variable responses to open-ended questions about suggestions to improve reports. Qualitative data will be analysed using content and thematic analysis techniques.

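### With four wards in two pairs at one site, ward differences cannot be adjusted for by ward-level covariates; the article should rely on each ward as its own control and say what stays unadjusted

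*Protocol article*

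**What the plan says.** The Setting and sample section fixes the number of clusters: "Four acute care wards will be included in the study". They are matched on casemix, and the abstract adds that "one ward from each pair is randomised to receive the intervention". The Methods section names the design: "This controlled interrupted time series study design incorporates two pairs of matched wards at an acute care hospital".

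Under Strengths and limitations of study, the article accepts that matching within one hospital may leave wards unlike, and gives as examples "differences in ward culture, patient acuity/type, staffing turnover". Its answer is "hence, we will adjust for differences using the available data".

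The Analysis section gives the only stated means. The chart-audit and RiskMan outcomes are rates, and "These data will be aggregated at ward level". The eight ACT dimensions, culture among them, are also aggregated by ward and entered as predictors of reporting rates. Then: "Multivariate regression analyses will include cluster correction to adjust for ward and site effect". The limitations section says that there is a single site.

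**The concern.** The limitations sentence offers adjustment as the remedy for imperfect matching. The differences it has in mind lie between wards, and there are only four wards to inform them. A characteristic that takes one value per ward cannot be told apart from the ward itself, and several such characteristics cannot be fitted alongside the arm.

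The risk is in how results would be labelled. A model on many ward-week rows can return a coefficient for a ward covariate, although that covariate has only four distinct values. The feedback effect could then be presented as adjusted for culture or turnover when it is not, and a shift in one ward could be read as a feedback effect or could hide one. The cluster correction does not cure this. It acts on standard errors rather than on confounding, and four clusters are a weak basis for it. A site effect has nothing to refer to at one site.

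**Working it through.** The article gives no power, alpha or effect size, so there is no stated figure to reproduce. The check is a count of what four wards can identify.

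**Inputs from the article**
- 4 wards, 2 pairs, 1 intervention ward per pair, 1 site.
- 8 ACT dimensions, measured at baseline and at 12 months.
- RiskMan: a report for the 12 months before the intervention, then weekly extraction for 12 months.
- Chart audit: 1 baseline point, then quarterly.

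**Step 1: covariates with one value per ward.** Residual degrees of freedom = 4 − rank of the design.

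| Terms | Columns | Rank | Residual df |
|---|---|---|---|
| mean, arm | 2 | 2 | 2 |
| mean, pair, arm | 3 | 3 | 1 |
| mean, pair, arm, 1 covariate | 4 | 4 | 0 |
| mean, arm, 2 covariates | 4 | 4 | 0 |
| mean, arm, 3 covariates | 5 | 4 | not estimable |
| mean, arm, 8 ACT scores | 10 | 4 | not estimable |

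The Analysis section names intervention dose rather than arm as the main predictor. Dose also takes one column, so the count does not improve. The two-sided 5% critical value of t is 4.30 with 2 df and 12.71 with 1 df.

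**Step 2: using both ACT waves.** There are 4 × 2 = 8 ward-by-wave cells. Ward effects (4), period (1) and arm by period (1) use 6 and leave 2. Adding 8 ACT scores gives 14 columns with rank 8. The second wave also follows the intervention. The pilot reported improved perceptions of evaluation and feedback mechanisms, so conditioning on that wave may remove part of the effect.

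**Step 3: the controlled time series.** The article states weekly extraction only for the intervention year. Assuming that the earlier year can also be split by week, there are 4 × (52 + 52) = 416 ward-weeks. Ward effects (4) plus time, post, time since start, and each of these by arm (6) give 10 columns with rank 10.
- Adding 8 baseline ACT scores: 18 columns, rank still 10. They are absorbed by the ward effects.
- Adding 2 covariates that vary by week within a ward: 12 columns, rank 12. These are estimable.

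**Step 4: what the pre-period removes and what it does not.** Assume a weekly residual SD of 1, a stable ward SD of 1, no true effect, and a ward-specific shift after the start with SD s. These values are not in the article. With two wards per arm:
- SD of the post-only arm contrast at s = 0: √(1 + 1/52) = 1.01 (simulated 0.98).
- SD of the difference in change: √(s² + 2/52).

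| s | SD by formula | SD simulated | Type I error, weekly rows taken as independent |
|---|---|---|---|
| 0 | 0.20 | 0.19 | 5.4% |
| 0.25 | 0.32 | 0.31 | 22% |
| 0.5 | 0.54 | 0.54 | 47% |

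Stable ward differences drop out of the difference in change. Ward-specific shifts do not.

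**The case against.** A reader might infer that the trial has no protection against ward confounding at all. The documents do not support that. Matching on casemix, randomisation within pairs and a controlled interrupted time series with 12 months of earlier RiskMan data on each ward need no covariates. In Step 4 they bring the spread of the arm contrast from about 1 down to about 0.2 when ward differences are stable.

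A reader might also infer that culture, acuity and turnover are to be fitted jointly as fixed covariates. The article lists them only as examples of how wards may differ. Acuity and turnover can vary over time, and if they are held by week they can be entered, as Step 3 shows. Which data and which model are details that an article may leave to a fuller plan. Nor does the article plan to treat weekly rows as independent, since it specifies a cluster correction; the last column of Step 4 therefore shows the size of the hazard and does not describe the stated analysis.

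All of this stands and narrows the point. It does not rescue the adjustment sentence for characteristics that sit at ward level, or the eight ward-aggregated ACT scores in the Analysis section. No fuller plan can make those estimable with four wards.

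**Conclusion.** The point holds in a limited form. Differences between wards cannot be adjusted for by ward-level covariates here. One ward-level degree of freedom is left after mean, pair and arm, or two without pair. Three ward covariates, or the eight ACT scores, are not estimable together with arm, and fixed characteristics add nothing once ward effects are in the time series. These counts follow from the stated design and rest on no assumed value. The weekly layout and the error rates in Step 4 do rest on assumptions and show mechanism and order of size only.

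Stable ward differences in the RiskMan outcome are handled by the design. Protection is weaker for the chart audit, where one baseline point allows a change from baseline but no pre-trend. Change over time peculiar to one ward is not handled for either outcome, beyond what covariates varying within a ward might capture. The article names no such covariates. The site effect conflicts with the single site. This should be corrected, but it does not invalidate the design.

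**What to change.** Replace the adjustment sentence under Strengths and limitations of study with wording such as:

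> Fixed differences between wards are handled by using each ward as its own control: for RiskMan reports, the level and slope in the 12-month pre-period; for the chart audit, change from the single baseline point, with no pre-trend available. The effect is shown as the within-pair difference in change, for each pair. Covariate adjustment is limited to routinely held quantities that vary over time within a ward. Differential change between wards over time cannot be adjusted for and remains a limitation.

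In the Analysis section, report the ward-aggregated ACT scores descriptively, rather than as joint predictors or as adjustment for confounding, and delete the site effect.

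The cost is analysis wording only; no data collection changes. The paper can no longer claim adjustment for ward culture or turnover, and its aim on organisational context becomes descriptive at ward level.

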### Dissemination and spread

This study will add new knowledge that will be of particular interest and relevance to health professionals and administrators. We will use a multi-faceted approach to disseminate the findings of this study to health professionals, administrators and policy-makers. We will present the results in journal articles and at local, national and international healthcare conferences. We will also communicate the findings through our formal and informal networks, nationally and internationally.

The partner organisation and members of the research team are committed to sharing new knowledge to promote safe, high-quality care delivery. Our findings will be disseminated through the collaboration’s existing networks, and a summary of the findings and information on the study, in a plain language format, will also be posted on the university website. Members of the research team sit on a range of policy decision-making committees and professional associations. As such, they have extensive networks for wide dissemination of the study findings.

### Study status

Data collection commenced in February 2015 and will finish in 2016. The data collection cycle is illustrated in Fig. 1.

## Discussion

This study has the capacity to make a significant contribution to the literature in terms of the efficacy of audit with feedback for nurses. Factors affecting reporting of medication errors will be clarified and will allow healthcare organisations to target quality programmes and feedback strategies to effect positive change. The theoretical basis and methodological design of this study integrates well-established theories and methods to comprehensively address the research questions. This intervention will potentially have wider application for the delivery of feedback to health professionals working in other settings, for other areas of preventable adverse events and to promote behaviour change in aspects of care such as use of clinical practice guidelines. These findings will inform development of future interventions, including system redesign, to prevent medication errors. This research has potential to inform initiatives to improve the quality and safety of care received by patients in the acute care setting and will also have significance internationally in the field of knowledge translation.

## Abbreviations

ACT: Alberta Context Tool
AE: Adverse event
PARIHS: Promoting Action on Research Implementation in Health Services
SMART: Safe Medication Audit Reporting Translation
TPB: Theory of Planned Behaviour
